**Methods:**

This randomized, double-blind, placebo-controlled clinical trial has completed ChiCTR registration. The trial will randomly divide 120 children who meet the inclusion criteria into three groups: experimental group 1 (basic treatment + Gegen Qinlian decoction granules + Erbai drink placebo), experimental group 2 (basic treatment + Erbai drink granules + Gegen Qinlian decoction placebo), and control group (basic treatment + Gegen Qinlian decoction placebo + Erbai drink placebo). The main efficacy indicators will be antibiotic use rate and clinical cure rate, and the secondary efficacy indicators will be time to antibiotic intervention, effective rate, and course of treatment determined after 5 days. The following physical and chemical indicators will be measured: routine blood parameters, procalcitonin, C-reactive protein, electrocardiogram, liver and kidney function, electrolytes, routine urinalysis, routine stool analysis, and stool culture (including drug sensitivity).

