### Eligibility criteria

#### Diagnostic criteria

The Western medicine diagnostic criteria for drug-resistant bacterial diarrhea in children are as follows [14, 15]:
Resistant bacteria found in the stool culture.Prerequisites: stool characteristics changed, showing loose, watery, mucus, or pus-blooded stools. Course of the disease within 2 weeks.Auxiliary conditions: stool frequency higher than usual, and at least three times a day, with or without abdominal pain, vomiting, and abdominal distension.

The TCM diagnostic criteria for diarrhea in children with damp-heat syndrome are as follows [16]:
Main symptoms: watery stools, or like egg-drop soup, urgent diarrhea, frequent doses, and foul smell.Secondary symptoms: sometimes some mucus, abdominal pain, nausea and vomiting, or fever, irritability, thirst, yellow urine, red tongue, yellow and greasy coating, slippery pulse, purple hand venules.

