#### Selection criteria

Age from 6 months to 14 years.Meet the Chinese and Western medicine diagnostic criteria, course of the disease within 2 weeks, and condition mild to moderate.White blood cell count in routine stool ≥ 5/high-power field (HPF), or increased procalcitonin, percentage of CRP or neutrophils, or total number of white blood cells in routine blood.Able to obtain consent from a guardian, fill in the informed consent form, and agree to participate (children > 8 years old should sign a consent form).

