#### Elimination criteria

Patients will be removed from the trial if they meet any of the following criteria:
After selection, the patient is found not to meet the selection criteria or to meet the exclusion criteria.Patients who fail to follow the protocol after selection.Patients with no post-treatment visit records after selection.

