One course of treatment for the above three groups will last 5 days, and one to two courses can be administered continuously. The specific observation time and related items are shown in Table 1.

**Table 1 Tab1:** Specific observation time and related items

Stage		Enrollment	Clinical observation time (days)									
**Date of visit**		**0**	**1**	**2**	**3**	**4**	**5**	**6**	**7**	**8**	**9**	**10**
**Case screening**		**√**										
**Sign informed consent**		**√**										
**Random entry group**		**√**										
**Delivery of test drugs**		**√**										
**CRF completed**		**√**	**√**	**√**	**√**	**√**	**√**	**√◎**	**√◎**	**√◎**	**√◎**	**√◎**
**Basic medical history**		**√**										
**General information**		**√**										
**General inspection items**	**Physical examination**	**√**	**√**	**√**	**√**		**√**	**√◎**	**√◎**	**√◎**	**√◎**	**√◎**
	**Routine blood test**	**√**	**◎**	**◎**	**√**	**◎**	**◎**	**√◎**	**√◎**	**√◎**	**√◎**	**√◎**
	**Procalcitonin**	**√**	**◎**	**◎**	**√**	**◎**	**√**	**◎**	**◎**	**◎**	**◎**	**◎**
	**C-reactive protein**	**√**	**◎**	**◎**		**◎**	**◎**	**√◎**	**√◎**	**√◎**	**√◎**	**√◎**
	**Electrocardiogram**	**√**					**√**	**√◎**	**√◎**	**√◎**	**√◎**	**√◎**
	**Liver and kidney function**	**√**					**√**	**√◎**	**√◎**	**√◎**	**√◎**	**√◎**
	**Electrolytes**	**√**					**√**					
	**Routine urine test**	**√**					**√**					
	**Routine stools**	**√**	**◎**	**◎**	**√**	**◎**	**√**	**√◎**	**√◎**	**√◎**	**√◎**	**√◎**
	**Stool culture (including drug sensitivity)**	**√**					**√**	**√◎**	**√◎**	**√◎**	**√◎**	**√◎**
**Stool characteristics**		**√**	**√**	**√**	**√**	**√**	**√**	**√◎**	**√◎**	**√◎**	**√◎**	**√◎**
**Stool frequency**		**√**	**√**	**√**	**√**	**√**	**√**	**√◎**	**√◎**	**√◎**	**√◎**	**√◎**
**Symptom evaluation**		**√**	**√**	**√**	**√**	**√**	**√**	**√◎**	**√◎**	**√◎**	**√◎**	**√◎**
**Temperature card**		**√**	**√**	**√**	**√**	**√**	**√**	**√◎**	**√◎**	**√◎**	**√◎**	**√◎**

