### Statistical analysis

Statistical analysis will be carried out using SAS 9.4 or above. According to the data characteristics, measured data will be analyzed by independent sample *t* tests or rank sum tests for comparison between groups and numerical data will be analyzed by χ^2^or Fisher’s exact probability tests. Laboratory data for all clinical endpoints will be analyzed according to intention to treat (ITT) and compliance (PP) analyses, and safety analysis will be performed using a safety data set (SS). The efficacy scores at the time of patient enrollment, intermediate follow-up (day 3, day 4 to day 7 after treatment), and at the end point of the trial will be calculated, and the mean, standard deviation, median, P5, P75, maximum and minimum values of the differences in values between baseline and the treatment period will be used. PP and ITT will be adopted to analyze the main index and overall index. Subjects with positive urine culture indicators will be included in the statistical subgroup to analyze the correlation between the study program and the overall efficacy evaluation index. Because this is a multicenter, randomized, double-blind controlled trial, the possible central effect on efficacy indicators should be considered.

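### The only stated subgroup rests on a urine culture that is never scheduled, and reading it as stool culture makes it the whole trial under the entry rule

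*Protocol article*

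**What the plan says.** **Subgroup (Statistical analysis).** "Subjects with positive urine culture indicators will be included in the statistical subgroup", in order to relate the study programme to the overall efficacy index. The same section applies both ITT and PP to the main index. The article states no other subgroup.

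**Measurements.** The abstract's Methods list ends with "routine urinalysis, routine stool analysis, and stool culture (including drug sensitivity" and a closing bracket. Table 1 has one urine row, "Routine urine test", ticked on days 0 and 5. It has one culture row, stool culture with drug sensitivity, ticked on days 0 and 5 and marked for days 6 to 10.

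**Entry.** The first Western diagnostic criterion is "Resistant bacteria found in the stool culture". The Selection criteria make it binding: "Meet the Chinese and Western medicine diagnostic criteria, course of the disease within 2 weeks, and condition mild to moderate".

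**Timing.** Table 1 has no column before day 0. Screening, consent, "Random entry group", drug delivery and the first stool culture all stand in that column.

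**Late ineligibility (Elimination criteria).** A child is removed from the trial if: "After selection, the patient is found not to meet the selection criteria or to meet the exclusion criteria".

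**Sample size.** 46% antibiotic use on either Chinese medicine against 80% on control, α = 0.05, n = 37 per group (111 in all), set at 120 with 10% drop-out in mind.

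**The concern.** A subgroup needs a classifying variable that the trial collects and that splits the randomised children. This one has neither property. Urine culture is not collected. The obvious substitute, a positive stool culture for a resistant organism, should be true of every child who satisfies the entry rule.

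It could split the sample only if some culture-negative children are randomised. The schedule allows that, because the entry culture is taken on the day of randomisation. But those children then fall under the elimination rule, so the plan would remove randomised participants on a result that became known only after allocation.

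Two things are at stake. First, someone must decide later what a positive culture means, with answers ranging from nobody to everybody. The Data management section unblinds the data before they reach the analysts, so that choice could be made with allocation known. Second, the plan does not settle whether culture-negative randomised children count in the primary analysis, and that affects both the ITT principle and the analysed sample size.

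**Working it through.** **1. The subgroup as written.** Urine tests scheduled: routine urine test only. Cultures scheduled: stool only. The abstract agrees with Table 1. Members identifiable from scheduled data: 0.

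**2. The subgroup read as baseline stool culture.**
- The Diagnostic criteria require a resistant organism in stool.
- The Selection criteria require the Diagnostic criteria to be met.
- With the rule enforced, positives = all eligible children = 120 of 120, or 40 per group. The subgroup equals the trial.
- With the rule not enforced at randomisation, a proper subset exists, but its complement is exactly the set of children that the Elimination criteria remove.

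Either way, no comparison of culture-positive with culture-negative children survives.

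**3. Where the removal would bite.** The day-0 culture is the only scheduled pre-treatment sample; the cultures from day 5 onwards come after treatment has begun and cannot establish entry. If the day-0 result returns after randomisation, a negative result is a failure to meet the selection criteria discovered after selection.

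**4. The plan's own sample size, reproduced.** Inputs: p1 = 0.80, p2 = 0.46, difference 0.34, mean 0.63, two-sided α = 0.05 (sidedness is not stated), power 0.80 (the article labels this figure β).
- Uncorrected: n = [1.960·√(2·0.63·0.37) + 0.842·√(0.80·0.20 + 0.46·0.54)]² / 0.34² = (1.338 + 0.538)² / 0.1156 = 30.4, so 31.
- Continuity-corrected: n' = (30.4/4)·[1 + √(1 + 4/(30.4·0.34))]² = 36.1, so 37, as stated.

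Because 37 reproduces with the continuity correction, Fisher's exact test is the closer like-for-like measure of power.

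**5. Illustration of the possible loss.** The documents give no positivity rate, so the fractions below are assumptions. Start from 40 per arm less 10%: 40 × 0.90 = 36. Multiply by the assumed positive fraction and find power for 80% against 46% by exact binomial enumeration, two-sided α = 0.05:

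| Assumed positive | Per arm | Fisher power |
|---|---|---|
| 100% | 36 | 80% |
| 90% | 36 × 0.90 ≈ 32 | 76% |
| 80% | 36 × 0.80 ≈ 29 | 69% |
| 65% | 36 × 0.65 ≈ 23 | 57% |
| 50% | 36 × 0.50 = 18 | 46% |

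An uncorrected χ² test is more favourable: 87% at 36 per arm, 83% at 32, 77% at 29 and 60% at 18. Fisher power is already at the 80% target after the planned drop-out, so it has no room for further removals; the χ² test has a little.

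**The case against.** The strongest reply is that "urine" is a one-word slip for "stool", and that the data for the intended analysis are collected on day 0 and again from day 5. It may well be a slip. But the corrected word gives a subgroup that coincides with the eligible population, so the slip cannot be cured by substitution alone.

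A second reply concerns timing. No turnaround time is given, recruitment is from both outpatient and inpatient departments, and the text does not exclude a routine culture done before day 0. This stands: the late-result problem is conditional. If every result is known before randomisation, no child is removed on this ground, but then the subgroup is redundant.

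Third, the Elimination criteria do not say which analysis set loses a removed child; the rule might touch only PP. That also stands, and is a reason to state it, because removal from the trial, taken literally, does not fit an ITT analysis.

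Three stronger readings are tempting and not supported:
- A reader might infer that the trial loses its only analysis of resistant diarrhoea. Under the entry rule, the ITT and PP analyses themselves address that population.
- A reader might infer that the trial is underpowered. The power figures rest on assumed positivity, and at 90% an uncorrected χ² test still exceeds 80%.
- A reader might infer that randomising on the Selection criteria alone removes the conflict. Those criteria themselves call in the resistant-culture requirement.

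**Conclusion.** The point holds as a contradiction between stated rules. Two parts need no assumption: the subgroup has 0 members as written, and read as stool culture it contains every eligible child. The third part is conditional. If the day-0 result arrives after randomisation and the elimination rule is applied to the ITT set, culture-negative children are lost after allocation, and the sample-size paragraph mentions only a 10% drop-out. How many would be lost cannot be derived from the article; Fisher power of about 76% to 46% for 90% to 50% positivity illustrates sensitivity and is not an estimate.

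Severity: should be fixed. The certain defect lies in a supportive subgroup and is cheap to correct, but the correction has to reach the entry, elimination and schedule rules as well as the one word.

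**What to change.** 1. In Statistical analysis, replace the urine-culture definition with a resistant organism on the day-0 (pre-treatment) stool culture.
2. Reconcile the Diagnostic criteria, Selection criteria, Elimination criteria and Table 1 by choosing one of two positions:
   - **Entry condition.** The resistant culture must be known before randomisation. Show the earlier culture in the schedule and delete the subgroup, which is then redundant.
   - **Classifier.** Children may be randomised before the result is known. Keep all randomised children in the ITT set whatever the culture shows, and analyse the resistant-culture group as a prespecified supportive analysis.
3. Make the choice before unblinding.

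**Cost.** The classifier option needs no new procedure, since the day-0 sample is already taken. It does need an amendment to the entry wording while recruitment is under way, and the ITT set may then include some culture-negative children. The entry-condition option needs a culture result before randomisation, and so a change to the visit schedule.

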### Setting and patients

A total of 120 children from the outpatient/inpatient departments of each participating center who meet the diagnostic criteria and inclusion criteria for bacterial diarrhea will be enrolled. The participating centers include the Children’s Diagnosis and Treatment Center of the Affiliated Hospital of Changchun University of Traditional Chinese Medicine, Shenzhen Children’s Hospital, and the First Affiliated Hospital of Hunan University of Traditional Chinese Medicine. The biological samples collected from the children must not be less than 2000. The children will be divided into three groups according to computer-generated random numbers, with a 1 in 3 probability of being allocated to any one group.

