#### Randomization and allocation

Taking the center as the unit, the patients were divided into an experimental group and a control group according to the stratified randomization principle. (Through the “central code allocation random number” sequence of SAS statistical software, the random code of each center is obtained, and the research center is randomly assigned through the random code.)

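### Randomisation is stratified by centre, but no centre-adjusted test is named for the primary proportions, and the allocation section misstates the number of groups and the unit assigned

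*Protocol article*

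**What the plan says.** **Analysis.** Under Statistical analysis, continuous outcomes are handled as follows: "measured data will be analyzed by independent sample *t* tests or rank sum tests for comparison between groups". Numerical data, which cover both primary outcomes (antibiotic use rate and clinical cure rate), are to be compared by χ² or "Fisher’s exact probability tests". None of these tests has a centre term. The section closes by noting that the trial is multicentre and that "the possible central effect on efficacy indicators should be considered". It names no method.

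**Allocation.** The Randomization and allocation section states: "Taking the center as the unit, the patients were divided into an experimental group and a control group according to the stratified randomization principle". The parenthesis that follows adds that "the research center is randomly assigned through the random code". Under Setting and patients, where three hospitals are named, the wording is different: it is the children who are split at random, into three groups, each child having a one-in-three chance of any given group. The abstract also divides 120 children at random into three groups, the Test drugs section describes three groups, and the Sample size section gives a 1:1:1 ratio.

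**The concern.** There are two separate faults.

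1. **Analysis does not follow the design.** Stratifying by centre balances the arms within each hospital. That removes between-centre variation from the treatment difference. A test with no centre term still counts that variation as noise, so its standard error is too wide whenever centre is prognostic, and the test rejects too rarely. Centre could well be prognostic here: the Test drugs section lets antibiotics be added if required, on a list of alternative signs, so the antibiotic-use endpoint depends partly on local judgement at three hospitals. At stake is some power, and a primary analysis whose handling of centre is left open.

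2. **The allocation text conflicts with the rest of the article.** The section that defines allocation names two groups where the trial has three, and it makes the research centre the thing assigned where other sections randomise children. A reader should not have to infer the randomisation unit of a randomised trial.

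**Working it through.** **Step 1. The plan's own figure.** Inputs from the Sample size section: antibiotic use 46% vs 80%, α = 0.05, power 0.80 (printed there as β), 1:1:1. The mean rate is 0.63 and the difference 0.34.

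- n₀ = [1.960·√(2·0.63·0.37) + 0.842·√(0.80·0.20 + 0.46·0.54)]² / 0.34² = 30.4, i.e. 31.
- With continuity correction: n = (n₀/4)·[1 + √(1 + 4/(n₀·0.34))]² = 36.1, i.e. 37.

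The stated 37 per group is reproduced (two-sided, continuity-corrected). It contains no centre term.

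**Step 2. Standard error without a centre term.** Assumptions: one TCM arm vs control, 37 per arm, split 13/12/12 over three centres and balanced within centre. The centre rates are assumed. Under the null, the test without a centre term uses the variance p̄(1 − p̄), while the true variance is the average of p(1 − p) within centres.

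- *Rates 95/80/65%.* p̄ = (13·0.95 + 12·0.80 + 12·0.65)/37 = 29.75/37 = 0.804. Overall variance 0.1576. Within-centre variance (13·0.0475 + 12·0.16 + 12·0.2275)/37 = 0.1424. SE ratio √(0.1576/0.1424) = 1.05. The effective critical value is 1.96·1.05 ≈ 2.06, so type I error is about 3.9%.
- *Rates 97/90/50%.* p̄ = 29.41/37 = 0.795. Overall variance 0.1631. Within-centre variance (13·0.0291 + 12·0.09 + 12·0.25)/37 = 0.1205. SE ratio 1.16. The effective critical value is about 2.28, so type I error is about 2.3% (2.2% by simulation).

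**Step 3. Simulation at the planned effect.** Uncorrected χ² against a Cochran-Mantel-Haenszel (CMH) test stratified by centre. A common odds ratio was chosen so that the overall difference stays at the planned 34 points.

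| Assumed control rates | Type I, χ² | Type I, CMH | Power, χ² | Power, CMH |
|---|---|---|---|---|
| 80/80/80% | 5% | 5% | 87% | 87% |
| 95/80/65% | 3.9% | 5% | 89% | 92% |
| 97/90/50% | 2.2% | 5% | 91% | 96% |

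A second set of runs used 40 per arm and centre log-odds of −b, 0, +b around the stated rates. Power was 90.9% vs 92.9% at b = 1 (control rates 64% to 93%) and 92.2% vs 95.6% at b = 1.5, with χ² type I error of 4.1% and 3.3%. Direction and order of size are the same.

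**Step 4. Allocation text side by side.**

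| Place | Groups | Unit |
|---|---|---|
| Abstract | three | children |
| Setting and patients | three | children |
| Test drugs | three | not addressed |
| Sample size | three, 1:1:1 | not addressed |
| Randomization and allocation | two | patients, then the research centre |

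The last row is the outlier on both counts, and on unit it also disagrees with itself.

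**The case against.** **The plan does not ignore centre, and the model may sit in an analysis plan not shown.** The first half is right: the closing sentence of Statistical analysis raises the centre effect. The second half carries weight too, since the list of tests by data type is generic. But the article names specific tests for the primary proportions and none of them uses the stratification factor, so an analysis plan that used a stratified test would depart from the tests named here. What remains is an improvement that costs nothing, not a serious error.

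**The centre rates are conjecture.** Correct. The article reports no variation between centres, and the same list of antibiotic triggers may keep hospitals close. The loss could be nil.

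**Stronger readings that the document does not support:**

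- *Centre is confounded with arm, so the trial is unanalysable.* The words about assigning the research centre invite this, with three centres and three arms. But the abstract and Setting and patients randomise children, and stratified randomisation of patients would mean nothing if whole hospitals were assigned. A separate random list for each centre is the natural meaning. Confounding and too-wide standard errors also cannot hold together: the first needs whole-centre assignment, under which a test without a centre term has standard errors that are too narrow.
- *Arm sizes would vary with an SD of about 5.2.* That assumes independent draws. The article never says so; a 1 in 3 chance is equally true of 1:1:1 blocks.
- *Power falls to 76% or 54%.* Those figures arise if the odds ratio implied by 46% vs 80% is held fixed while centre rates are spread. The overall difference then shrinks from 34 points to about 28 or 22, and that explains most of the fall.

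**Conclusion.** The point holds in a limited form. Randomisation is stratified by centre, and the article commits to no analysis that uses centre. If children are randomised within centre and centre is prognostic, the named tests are conservative. For the two assumed spreads the standard error is about 5% or 16% too wide under the null, type I error is 3.9% or 2.2% in place of 5%, and power is about 3 to 6 points lower than a centre-stratified test would give. Power stays above the planned 80% in every scenario that holds the 34-point difference, and there is no bias and no inflated error. With no centre effect the two tests perform alike.

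The contradiction over the number of groups and the unit assigned rests on the text alone and needs no assumption. It is most likely a drafting fault. It is not evidence that hospitals were allocated to arms.

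**What to change.** 1. **Statistical analysis.** Make the primary comparison of each TCM arm with control a Cochran-Mantel-Haenszel test stratified by centre, reported with a Mantel-Haenszel risk difference and confidence interval. This replaces the open sentence on centre effects with a method. The stated 37 per group need not change.
2. **Randomization and allocation.** Rewrite to say that individual children are randomised 1:1:1 to the three arms within each centre, if that is what was done, and check the wording against the SAS code lists actually generated. Align Setting and patients with it.

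Both are changes of wording, with no extra patients or data. The Data management section has unblinding follow data lock, so the test should be fixed before then.
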